#### Intervention Group only—training in GP-nurse team management of newly-diagnosed COPD

In practices randomized to the GP-practice nurse partnership management arm, the nurses and GPs will attend further workshops to receive practical training in team-based management of COPD. These additional workshops for GPs and practice nurses in the GP-practice nurse partnership intervention will be provided by the study team including a nurse academic, a GP academic, and a respiratory physician. The intervention workshops will comprise a full day for practice nurses, a distance learning activity for GPs, and an evening workshop for both practice nurses and GPs.

The one-day training workshop for nurses will cover: pathophysiology and assessment of COPD; smoking cessation including use of lung age as a motivational tool [27]; COPD management according to Australian guidelines [17]; prescribing guidelines; assessment of patients’ inhaler technique and education to improve technique [43]; the role of pulmonary rehabilitation; the management of exacerbations; the use and value of nurse/GP joint care planning; information about reimbursement codes for relevant activities; and education about self-efficacy theory, motivation, change management, teamwork, and fostering partnerships. The program will be based on that used in an earlier study [44], with adaptation to address specific issues for patients with newly-diagnosed COPD. It will foster a culture of positive organisational change through team building and promotion of collaborative practice [45]. Practice nurses will be provided with a folder containing workshop notes and presentations.

GPs will complete a computer-based distance learning activity and quiz on the management of COPD according to the COPDX guidelines. The evening three-hour workshop for GPs and practice nurses will focus on the importance for each GP-practice nurse team to clarify individual elements of their roles, because lack of understanding has been shown to be a barrier to collaborative practice [46,47]. Each practice will be provided with a copy of current Australian COPD guidelines [17].

#### Control group training

After case-finding training, practices that are randomized to usual care will be provided with a print copy of the Australian COPD guidelines [17]. At the end of the study, after conclusion of all data collection for all practices, GPs and practice nurses in the control group will be offered a workshop on assisting patients to optimise their inhaler technique.

#### Intervention group—delivery of GP-Practice nurse team management for newly-diagnosed COPD

In the intervention practices, the practice nurse will work in partnership with the GP and patient to develop a care plan for patients newly-diagnosed as having COPD. The workbooks provided during the intervention group training workshops will prompt the nurse and GP to include relevant components of the following in the care plan:

1. Smoking cessation: advice based on Smoking Cessation Guidelines for Australian General Practice [50].

2. Immunization: influenza and pneumococcal vaccination status will be assessed relative to local guidelines [51], and immunization recommended and provided where appropriate.

3. Exercise: recommendation about regular exercise for all patients regardless of COPD severity; patients with moderate or severe COPD provided with details of their local pulmonary rehabilitation provider.

4. Medication review: review of current medications and education about potential future indications for pharmacotherapy. For patients already using any inhaler, inhaler technique will be checked using published checklists [43]. Patients for whom inhaled medication is indicated will be educated on the appropriate use of these using established protocols [43].

5. Nutrition: Advice about diet and exercise and referral to a dietician if appropriate for overweight or underweight patients.

6. Psychosocial issues: identification and management of anxiety and/or depression.

7. Co-morbidities and complications of COPD will be assessed and managed.

8. Patient education: patients will be provided with written information about COPD (from Australian Lung Foundation http://www.lungfoundation.com.au/) and its management and with information about local patient support groups which provide emotional support and self-management information.

The nurse and GP will work in partnership with the patient to implement care plans using appropriate prescribing, investigations, referral, and follow-up consultations with the GP, and visits or telephone consultations with the practice nurse. Patients will be added to a COPD Register within the practice to facilitate appropriate recall and reminder notifications and monitor patient progress. This will allow recording of implementation milestones in patient care plans, outstanding actions, and review arrangements. The guideline-based care plan for each patient will seek to optimise management, improve function, prevent deterioration, and enhance patient knowledge and skills. It may be informal, or may be documented in line with government-funded reimbursement programs for chronic disease care [32].

#### Control group: usual care for newly-diagnosed COPD

In the control practices, at the completion of the case-finding visit, the nurse will recommend that patients with newly-diagnosed COPD should see their GP for management of the condition. Usual care for the purpose of this study will thus be the normal pattern of care of COPD by the GP; to ensure that all GPs have access to current Australian COPD guidelines, they will be provided with a print copy [17]. All current smokers will be offered brief smoking cessation advice at the case-finding visit, regardless of the results of spirometry.

#### Intervention and control groups: mentoring of practice nurses

Brief periodic mentoring will be provided to all practice nurses by experienced registered nurses in order to facilitate compliance with study processes, to enhance recruitment and retention of patients, and to provide a standardised framework for responding to questions. Intervention and control practices will receive similar levels of spirometry mentoring. Intervention practices alone will receive mentoring relating to GP-nurse case management of COPD. Mentoring of intervention and control practices will be carried out by two different registered nurses to avoid any cross-contamination between randomisation groups.

### Outcome measures

#### Data collection—patients

Once the project officer has received the consent form, contact details, and spirometry worksheet for a patient, they will arrange a visit as soon as possible for baseline assessment, either at the patient’s home or at the GP’s practice according to patient preference. The project officer will collect demographic data including age, gender, body mass index, employment status, education, and country of birth, and data for outcome and process measures. Further data collection will occur at 6 months (by telephone and mail) and 12 months (face to face).

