**Design:**

A pragmatic cluster randomised trial will test the hypothesis that intervention by a practice nurse-general practitioner (GP) team leads to improved health-related quality of life and greater adherence with clinical practice guidelines for patients with newly-diagnosed COPD, compared with usual care. Forty general practices in greater metropolitan Sydney Australia will be recruited to identify patients at risk of COPD and invite them to attend a case finding appointment. Practices will be randomised to deliver either practice nurse-GP partnership care, or usual care, to patients newly-diagnosed with COPD.

The active intervention will involve the practice nurse and GP working in partnership with the patient in developing and implementing a care plan involving (as appropriate), smoking cessation, immunisation, pulmonary rehabilitation, medication review, assessment and correction of inhaler technique, nutritional advice, management of psycho-social issues, patient education, and management of co-morbidities.

The primary outcome measure is health-related quality of life, assessed with the St George’s Respiratory Questionnaire 12 months after diagnosis. Secondary outcome measures include validated disease-specific and general health related quality of life measures, smoking and immunisation status, medications, inhaler technique, and lung function. Outcomes will be assessed by project officers blinded to patients’ randomization groups.

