#### Outcome measures—patients

The primary outcome measure will be disease-specific quality of life assessed by the St George’s Respiratory Questionnaire (SGRQ [52]). Secondary outcome measures include: patient awareness of COPD diagnosis, COPD Assessment Test (CAT, a disease specific QOL measure [53]); smoking status by self-report and from carbon monoxide analysis (Smokerlyzer, Bedfont Scientific Ltd, Maidstone, UK) and readiness to quit if applicable; immunisation rates; medication including appropriate inhaler prescription and effective inhaler use; referral for pulmonary rehabilitation or referral for or provision of exercise prescriptions; disease related knowledge [54]; patient satisfaction; healthcare utilisation; and lung function. The relationship between objectives, outcomes, measures, and hypothesis is outlined in Table 1.

**Table 1 T1:** Relationships between objectives, outcomes, measures and hypotheses

**Objective**	**Hypothesis**	**Outcome**	**Measure**	**Visit**
To assess the effectiveness of early intervention by a GP-practice nurse partnership, in patients newly identified as having COPD	Early intervention by a GP–practice nurse partnership will improve outcomes for patients with COPD, compared with usual care	Improvement in disease related quality of life	St George’s Respiratory Questionnaire (SGRQ) [52]	1,2,3
			COPD Assessment Test (CAT)	1,2,3
		Improved smoking cessation rates	Participation in smoking cessation program; quit rates (self-report)	1,2,3
			Validation of smoking cessation (where applicable) by carbon monoxide analysis	1,3
		Improved compliance with COPD immunisation recommendations	Influenza and pneumococcal vaccination status (self-reported)	1,3
		Improved prescribing and use of medications for COPD	Audit of prescribing against COPD-X guidelines	1,2,3
			Inhaler technique score using published checklists [43]	1,3
		Increased referral for pulmonary rehabilitation	Completion of pulmonary rehabilitation (self-reported)	1,2,3
		Increase in disease related knowledge	COPD knowledge questionnaire score [54]	1,3
		Improved general health status	General health status question (using preliminary question from SGRQ) [52].	1,2,3
		Slower decline in lung function	Post-bronchodilator FEV_1_	1,3
To assess the acceptability and feasibility of team-based vs conventional management of patients with COPD		Improved team-work between GP and practice nurse	Collaborative Practice Scale, VAS scale for team management of COPD	End of study

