#### Sample size calculations

The sample size calculation is based on a minimum clinically important difference for the primary outcome measure (SGRQ) of 4.0 [52], between subject standard deviation in SGRQ of 13 in a similar population [54], intra-cluster correlation coefficient of 0.01, and a resultant design effect of 1.09 for a cluster size of 10. With this design effect, a sample size of 200 patients completing each arm will provide >80% power to detect a difference of 4 or greater in SGRQ (calculations in PASS software). Forty practices will each invite 300 patients to attend a case-finding appointment, and within each practice this is expected to produce 12 patients with a new diagnosis of COPD; loss to follow-up of 20% by 12 months has been assumed. The projected recruitment rate is derived from the response rate to invitation (25%), and the yield of new diagnoses (21%) in our recently completed case-finding project [10].

This sample size will also confer 90% power to identify a doubling of the expected rate of correct inhaler use (from 20% to 40%) at a significance level of 5% (based on an ICCC of 0.1, and design effect of 2.1).

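### No remote route is named for the primary 12-month SGRQ when the face-to-face visit fails, although SGRQ is already collected by telephone and mail at 6 months

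*Protocol article*

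**What the plan says.** All references are to the Protocol article.

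- **Primary endpoint** (abstract, Design): health-related quality of life, "assessed with the St George’s Respiratory Questionnaire 12 months after diagnosis".
- **Mode of follow-up** (Data collection—patients): "Further data collection will occur at 6 months (by telephone and mail) and 12 months (face to face").
- **Place of visit** (same section): the baseline assessment takes place "either at the patient’s home or at the GP’s practice according to patient preference". The place of the 12-month visit is not given.
- **SGRQ schedule** (Table 1): "St George’s Respiratory Questionnaire (SGRQ) [52] 1,2,3". Visit 2 is the 6-month telephone and mail contact.
- **Items that need the patient present** (Table 1): carbon monoxide analysis, inhaler technique and post-bronchodilator FEV1 (the outcome labelled "Slower decline in lung function") are scheduled at visits 1 and 3 only. All are secondary.
- **Expected loss** (Sample size calculations): "loss to follow-up of 20% by 12 months has been assumed".
- **Analysis** (Data analysis): a mixed model with time and treatment group as fixed effects, and practice and subject within practice as random effects.

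**The concern.** The primary endpoint is a questionnaire, and the trial is already set up to take it without a visit. At the time point that decides the trial, the stated mode is a visit, and no alternative is named for a patient who has moved away, is too unwell or declines. As described, such a patient contributes no observed 12-month SGRQ, even if willing to fill in a form. What calls for a visit is a set of secondary measures.

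Two things are at stake. One is precision on the primary comparison, where the expected number of completers already falls slightly below the stated requirement. The other is reliance on an untestable assumption: the more 12-month scores are missing, the more the estimate depends on their being missing at random given the baseline and 6-month scores. Patients who deteriorate or disengage after month 6 may not meet that assumption.

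**Working it through.** **Inputs** (Sample size calculations): "minimum clinically important difference for the primary outcome measure (SGRQ) of 4.0"; "between subject standard deviation in SGRQ of 13 in a similar population"; intra-cluster correlation 0.01; cluster size 10; 200 completers per arm; 40 practices; 12 new diagnoses per practice; 20% loss. Assumed: equal allocation (20 practices per arm) and two-sided 5% significance. The article states 5% only for the inhaler-use calculation.

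**1. Reproduce the stated power.** Design effect = 1 + (10 − 1) × 0.01 = 1.09. Effective sample = 200 / 1.09 = 183.5 per arm. A two-sample comparison with difference 4 and SD 13 has power 83.8%, which agrees with the stated figure of more than 80%. The minimum for 80% is 166 × 1.09 ≈ 181 completers per arm.

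**2. Expected completers.** Recruited: 40 × 12 = 480. Lost: 480 × 0.20 = 96. Completers: 480 − 96 = 384, or 192 per arm, which is 400 − 384 = 16 fewer than stated. (480 is 400 × 1.2; allowing for 20% loss needs 400 / 0.8 = 500.) Recovering 16 of the 96, one sixth, would restore 400.

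**3. Effect of recovering some losses.** The documents do not say what share of non-attenders would return a form, so the share is varied. With 240 recruited per arm, n = 240 × (1 − loss), cluster size m = n / 20, design effect = 1 + (m − 1) × 0.01, and SE = 13 × √(2 × design effect / n).

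| Share of losses recovered (assumed) | Loss | n per arm | Design effect | SE of difference | Power |
|---|---|---|---|---|---|
| None (as planned) | 20% | 192 | 1.086 | 1.38 | 82.5% |
| One quarter | 15% | 204 | 1.092 | 1.35 | 84.5% |
| One half | 10% | 216 | 1.098 | 1.31 | 86.3% |
| All (upper bound, not attainable) | 0% | 240 | 1.110 | 1.25 | 89.2% |

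The last row is a ceiling only: loss to follow-up can include deaths, withdrawn consent and untraceable patients, whom no form reaches. These figures count completers at 12 months and give no credit for what the mixed model takes from earlier scores, so they overstate the gain if anything.

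**4. Bias.** No calculation is offered. It would need the SGRQ gap between non-attenders and attenders in each arm, and the document gives no figure for either.

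**The case against.** The strongest reply is that the article states a planned mode and nothing more. It does not say face to face only, does not forbid another route, and has no rule that a missed visit forfeits the SGRQ. A condensed article commonly leaves missed-visit procedures to the full protocol. This stands: a reader might infer that remote collection at 12 months is ruled out, and the text does not support that.

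Second, the visit may be easier to keep than it looks. Project officers, not the practices, collect the data. Patients consent to release of their contact details, and home visits are offered at baseline. Leaving the practice is therefore a weak cause of loss, and nothing makes SGRQ conditional on accepting the breath tests. This also stands, though it does not help a patient who has moved far away or refuses any visit.

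Third, a reader might infer that loss will differ by arm because only the description of intervention care includes a recall and reminder register. The document does not establish this. The register is a clinical tool, research visits are arranged by project officers blinded to allocation, and mentoring aimed partly at patient retention goes to nurses in both arms. Differential attendance is possible in a trial where patients know their group, but it cannot be sized from the document.

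Fourth, the mixed model can use baseline and 6-month scores, the 20% loss is budgeted, and the same mode at baseline and 12 months is a sound reason to prefer a visit. All true. But the model covers the gap only under missing at random, and an observed score needs less assumption than a modelled one. By taking SGRQ remotely at 6 months, the design already accepts both modes.

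**Conclusion.** The point holds as a modest, inexpensive improvement to a stated design choice. It is neither an error nor a contradiction. The article gives face to face as the mode for the primary 12-month SGRQ and names no remote fallback, while running the needed route six months earlier.

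The size is small. Planned power stays above 80% without any change. The gain is about 2 percentage points if a quarter of the losses are recovered and about 4 if half are, and these recovery rates are assumptions. Recovering one sixth would close the 16-patient gap to the stated 400. The other benefit, less reliance on missing at random, is real but cannot be quantified here. If the full protocol already provides a fallback, only a clarification is needed.

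**What to change.** In Data collection—patients, keep face to face as the default at 12 months and add that patients who decline or cannot have the visit will be asked to complete the SGRQ, and the other questionnaire items already collected at visit 2 (such as CAT and self-reported smoking), by mail or telephone. Vaccination status is not a visit 2 item in Table 1, so collecting it this way would need a small addition to the 6-month forms. Record the mode for every 12-month SGRQ, include the remote scores in the primary analysis, and repeat that analysis without them as a sensitivity check.

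The cost is a sentence, a mode field and some extra follow-up by project officers who already run the 6-month contact. The downside is that a minority of 12-month scores come by a different mode from baseline, possibly in unequal numbers by arm, which is why the mode is recorded and the sensitivity analysis is needed. Carbon monoxide, inhaler technique and FEV1 remain missing for these patients.

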#### Outcome measures—patients

The primary outcome measure will be disease-specific quality of life assessed by the St George’s Respiratory Questionnaire (SGRQ [52]). Secondary outcome measures include: patient awareness of COPD diagnosis, COPD Assessment Test (CAT, a disease specific QOL measure [53]); smoking status by self-report and from carbon monoxide analysis (Smokerlyzer, Bedfont Scientific Ltd, Maidstone, UK) and readiness to quit if applicable; immunisation rates; medication including appropriate inhaler prescription and effective inhaler use; referral for pulmonary rehabilitation or referral for or provision of exercise prescriptions; disease related knowledge [54]; patient satisfaction; healthcare utilisation; and lung function. The relationship between objectives, outcomes, measures, and hypothesis is outlined in Table 1.

**Table 1 T1:** Relationships between objectives, outcomes, measures and hypotheses

**Objective**	**Hypothesis**	**Outcome**	**Measure**	**Visit**
To assess the effectiveness of early intervention by a GP-practice nurse partnership, in patients newly identified as having COPD	Early intervention by a GP–practice nurse partnership will improve outcomes for patients with COPD, compared with usual care	Improvement in disease related quality of life	St George’s Respiratory Questionnaire (SGRQ) [52]	1,2,3
			COPD Assessment Test (CAT)	1,2,3
		Improved smoking cessation rates	Participation in smoking cessation program; quit rates (self-report)	1,2,3
			Validation of smoking cessation (where applicable) by carbon monoxide analysis	1,3
		Improved compliance with COPD immunisation recommendations	Influenza and pneumococcal vaccination status (self-reported)	1,3
		Improved prescribing and use of medications for COPD	Audit of prescribing against COPD-X guidelines	1,2,3
			Inhaler technique score using published checklists [43]	1,3
		Increased referral for pulmonary rehabilitation	Completion of pulmonary rehabilitation (self-reported)	1,2,3
		Increase in disease related knowledge	COPD knowledge questionnaire score [54]	1,3
		Improved general health status	General health status question (using preliminary question from SGRQ) [52].	1,2,3
		Slower decline in lung function	Post-bronchodilator FEV_1_	1,3
To assess the acceptability and feasibility of team-based vs conventional management of patients with COPD		Improved team-work between GP and practice nurse	Collaborative Practice Scale, VAS scale for team management of COPD	End of study
		Barriers and facilitators to team-work management of COPD	Process measures relating to GP and PN visits.	1, 2, 3
			Semi-structured interviews with GPs, PNs, patients	End of study

#### Process measures

At each visit/telephone call, patients will be asked the number of times they have visited the GP and/or practice nurse (total, and COPD-related), and the COPD-related areas addressed. At the end of the study, GPs and practice nurses in both groups will be asked to rate the extent to which they practice team-based management of COPD, on a visual analogue scale. Practice nurses and GPs will complete the Collaborative Practice Scale [55] to assess the ‘interactions between nurses and GPS that enable the knowledge and skills of both professionals to synergistically influence patient care’ [55].

Semi-structured interviews at the conclusion of the project with the practice nurses, GPs, and patients will examine satisfaction with the program and will explore the effects and value of the nurse input into COPD diagnosis and care, and barriers and facilitators to the team-management approach. The software package NVivo® will be used to facilitate coding and exploration of the data.

